## Abstract

**Background::**

Postoperative gastrointestinal dysfunction (PGD) refers to one of the common postoperative complications. Acupuncture can facilitate the recovery of PGD, whereas no therapeutic schedule of acupuncture has been internationally recognized for treating PGD. In the present study, a scientific trial protocol has been proposed to verify the feasibility of acupuncture in treating gastrointestinal dysfunction after laparoscopic cholecystectomy under general anesthesia. We conduct this protocol to investigate whether acupuncture recovery gastrointestinal dysfunction by influencing the expression of gastrointestinal hormone.

**Method::**

The present study refers to a randomized, evaluator blinded, controlled, multi-center clinical trial; it was designed complying with the Consolidated Standards of Reporting Trials (CONSORT 2010) as well as the Standard for Reporting Interventions in Controlled Trials of Acupuncture (STRICTA). The subjects will be taken from the inpatients having undergone laparoscopic surgery of Mianyang Affiliated Hospital of Chengdu University of traditional Chinese medicine, Mianyang Third Hospital and Mianyang Anzhou Hospital. Based on the random number yielded using SPSS 25.0 software, the qualified subjects will be randomly classified to the experimental group and the control group. Therapies will be performed 30 min once after operation, the experimental group will be treated with acupuncture, while the control group will receive intravenous injection of granisetron. The major outcome will be the time to first flatus, and the secondary outcomes will include the time to first defecation, abdominal pain, dosage of analgesia pump, abdominal distention, nausea, vomiting, gastrointestinal hormone, as well as mental state. The efficacy and safety of acupuncture will be also assessed following the principle of Good Clinical Practice (GCP).

**Discuss::**

A standardized and scientific clinical trial is conducted to assess the efficacy and safety of acupuncture for gastrointestinal dysfunction after laparoscopic cholecystectomy under general anesthesia. The aim is to objectively evidence and improves the clinical practice of acupoint prescription, as an attempt to promote the clinical application of this technology.

## Introduction

1

Postoperative gastrointestinal dysfunction (PGD) refers to a common postoperative complication, capable of causing many clinical symptoms (e.g., nausea, vomiting, abdominal pain, bloating, constipation, as well as diarrhea).^[1]^ PGD is likely to cause intestinal paralysis, acute gastric dilatation, and obstructions in severe cases, thereby affecting patients’ quality of life and prolonging the hospital stay of the patient.^[2]^ The specific mechanism of PGD remains unclear. It has been known that PGD is tightly associated with general anesthesia, gastrointestinal hormones, electrolyte disturbance, as well as abdominal inflammation.^[3]^ For the routine treatment of PGD, fasting, enema, oxygen inhalation, analgesia, fluid supplement, acid–base regulation, infection prevention, as well as gastrointestinal decompression are covered.^[4]^ Granisetron, domperidone, cisapride, and everypan refer to the typical drugs for PGD. Domperidone and cisapride are likely to induce adverse reactions of cardiovascular system; granisetron can cause fever and headache, and side effects of nausea and vomiting may be attributed to evermopan.^[5]^ As reported in the mentioned literature, the side effects and potential risks of these drugs limit their wide application.

Over the past few years, Enhanced recovery after surgery (ERAS)^[6]^ (i.e., applying all types of evidence-based therapies in the perioperative period to mitigate surgical complications, expedite postoperative recovery and shorten hospital stay of the patients) has aroused increasing attention by surgeons; acupuncture has been considered a part of ERAS by some researchers and has been progressively applied in treating postoperative complications.^[7,8]^ In 1998, the National Institutes of Health issued a consensus statement that acupuncture can act as a feasible treatment for postoperative nausea and vomiting.^[9]^ Acupuncture refers to an alternative therapy of traditional Chinese medicine (TCM), numerous experimental and clinical studies reported that acupuncture has a significant two-way regulatory effect on the movement, secretion and absorption of the digestive system.^[10,11]^ By stimulating nerves, especially vagus nerve, acupuncture can achieve the regulating effect on gastrointestinal function.^[12]^ Lu^[13]^ reported that electroacupuncture at *Zusanli* (ST36) regulated gastric motility in rats by vagus and sympathetic reflex, mediated by M2/3 and β1/2 receptors, respectively; in this procedure, vagus reflex played a major role. As suggested in a clinical research,^[14]^ acupuncture at *Zusanli* (ST36) can stimulate the peroneal nerve, and subsequently the pulse signal was transmitted to the vagus nerve via the sciatic nerve, release the 1-amino acid decarboxylase to elevate the neurotransmitter level. As revealed from an experimental research,^[15]^ electroacupuncture at *Neiguan* (PC6) can stimulate the sensory fibers of the median nerve and subsequently stimulate the solitary tract nucleus of the vagus nerve, so the neurotransmitters were release. As the research regarding gastrointestinal diseases has been leaping forward, a growing number of scientists believe that gut and brain are closely related, and the brain-gut axis links central nervous system and gastrointestinal tract.^[16]^ Signals from the brain are capable of affecting gastrointestinal motility, whereas information transmitted from the gastrointestinal tract can affect brain function as well.^[17]^ Brain-gut peptide refers to a type of small molecular peptide with double distribution in gastrointestinal tract and brain, being critical to gastrointestinal motility.^[18]^ Peripheral ghrelin has been suggested to be vital to regulate gastrointestinal function, while ghrelin in central nervous system can considerably affect gastrointestinal activity.^[19]^An experiment also suggested that electroacupuncture can reduce auxin and neuropeptide Y in rats and reduce their food intake.^[20]^ Excessive release of 5-hydroxytryptamine (5-HT) and substance P (SP) from gastrointestinal tract might cause intestinal dysfunction, while scalp acupuncture can down-regulate the expression level of 5-HT and SP in irritable patients to facilitate the recovery of gastrointestinal function.^[21]^

Some systematic reviews have also verified the feasibility of acupuncture for PGD and have drawn a positive conclusion.^[22,23]^ For the defects of research quality, statistics and research methods, the clinical results should be interpreted rigorously, and their scientific basis remain insufficient.^[24]^ Scalp acupuncture is a part of acupuncture therapy to treat diseases by stimulating specific location of the head area, showing a considerable effect on numerous diseases resulting from the brain.^[25]^ The acupuncture prescriptions for PGD primarily involve the points located in trunk and limbs.^[26]^ In the present clinical trial, the acupoints in the head area will be chosen in accordance with brain-gut axis theory, which is a novel exploration and attempt to apply acupuncture for PGD. By referencing to the design of similar studies,^[27]^ 18 patients having undergone laparoscopic surgery were pre-tested strictly following the evaluation and treatment process of this study. These subjects were randomly classified to “experimental group” (acupuncture) and “control group” (granisetron); the experimental group (16.31 ± 2.21 h) had a shorter average time to first flatus than the control group (26.14 ± 3.53 h). According to the preliminary results, acupuncture can effectively relieve gastrointestinal dysfunction after laparoscopic cholecystectomy.

## Methods

2

### Trial design

2.1

This study refers to a randomized, evaluator blinded, controlled, multi-center clinical trial to be conducted in Mianyang Affiliated Hospital of Chengdu University of TCM, Mianyang Third Hospital, Mianyang Anzhou Hospital, China. Eligible participants will be randomly classified into the experimental group (n = 90) and the control group (n = 90) at a ratio of 1:1. The patients will receive one of the following interventions 30 min after laparoscopic cholecystectomy, which are acupuncture and intravenous injection of granisetron. The results will abide by the Consolidated Standards of Reporting Trials (CONSORT)^[28]^ guidelines as well as Standards for Reporting Interventions in Clinical Trials for Acupuncture (STRICTA)^[29]^ and Standard Protocol Items: Recommendations for Interventional Trials (SPIRIT) guidelines.^[30]^ This study (protocol version 2.0, May 25, 2018) was registered at the Chinese Clinical Trials Registry (ChiCTR-1800016991). Figure 1 illustrates the research design and Figure 2 presents the trial schedule.

**Figure 1 F1:**
[figure not shown]
Participant flow diagram.

**Figure 2 F2:**
[figure not shown]
SPIRIT schedule of schedule of enrollment, interventions, and assessments. t1 is the day before surgery, t0 is the day of the surgery, t1 is 0 to 2 h after surgery, t2 is 2 to 6 h after surgery, t3 is 6 to 12 h after surgery, t4 is 12 to 24 h after surgery, t5 is 24 to 48 h after surgery, t6 is the day of the discharged, t7 is 2 weeks after patients discharged from the hospital.

### Participants

2.2

All subjects will be diagnosed by two surgical experts and one anesthesiologist in accordance with the inclusion and exclusion criteria. The potential participants meeting all the inclusion criteria and match none of the exclusion criteria should communicate with the research assistant about the study face to face. The research assistant will conduct a series of disease assessment and safety assessment to eligible patients interested in the study. After signing the informed consent, subjects will be randomly split into two groups and received different treatment.

### Recruitment

2.3

During the study, three research assistants should go to the general surgery department of the research centers three times a week to screen out subjects. Eligible patients will be identified and invited to the study. The research assistants will provide written informed consent to the patient and elucidate the details of the study (e.g., objective, scope, procedure, potential benefits, and risks). The patient will sign the informed consent in the presence of the research assistants who can also accept oral informed consent if the participants are unable to read.

### Inclusion criteria

2.4

Subjects will be included if meeting all the following criteria of the study:

1.the age between 18 and 70 years;2.the operation type is laparoscopic cholecystectomy, and the anesthesia type is general anesthesia, complying with the I to II classification standard of American Society of anesthesiologists;3.the intravenous analgesia pump will be employed postoperatively;4.the operation time is 2 ± 1. 0 h;5.having not undergone any other clinical trials during this study;6.without any cognitive impairment, aphasia, mental disorder, and other communication barriers;7.having participated in the trial and sign the informed consent voluntarily.

### Exclusion criteria

2.5

Subjects will be excluded if meeting any of the following criteria:

1.obesity (body mass > 80 kg), during pregnancy and lactation, with a fertility or pregnancy plan within recent 3 months;2.with severe cardiovascular disease, central nervous system disease, diabetes mellitus, as well as psychosis;3.administrated with gastric motility drugs within 24 h before operation or gastric tube keeping after operation;4.with severe gastrointestinal disease or previous history of PGD;5.averse to acupuncture treatment, or have aphasia, audio-visual disorders;6.with intraoperative blood loss ≥1000 mL or hemoglobin <70 g/L;7.with the history of drug abuse.

### Elimination standard

2.6

Subjects will be eliminated from the trial if meeting any of the following conditions:

1.laparoscopy must be converted to laparotomy;2.refusal to continuous treatment for various reasons;3.with severe syndromes (e.g., biliary fistula and peritonitis) during the treatment;4.transferred to other specialist treatments;5.having become comatose or die;6.cannot participate in the follow-up for various reasons;7.researchers accidentally included the subjects not meeting the inclusion criteria;8.less compliance with the treatment regulations and failed to provide information that might be critical to the evaluation.

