#### Statistical analysis

2.15.2

1.Analysis procedures sample distribution: The number of dropouts and the rate will be described and analyzed for each data set, and the reasons for any dropouts are elucidated.2.Balance comparison: The subjects’ general data will be compared to assess the comparability of the two groups.3.Efficacy analysis: The subjects’ time to first flatus will be used as the primary outcome measure to assess the efficacy and safety of acupuncture in treating PGD. The means (χ) and standard (SD) deviations will be calculated to express the outcome measure, and the experimental and control groups will be statistically compared by two independent-sample *t* tests. Eight secondary outcomes will be applied to assess the efficacy of the acupuncture. Seven of these—namely, time to first defecation, abdominal pain, dosages of analgesia pump, abdominal distention, nausea, vomiting, and gastrointestinal hormones will be described usinḡχ± SD deviation and statistically compared between groups by Repeated Measures Analysis of Variance (RMANOVA). The statistical analysis of time to first defecation will be identical to that of time to first flatus. However, before performing RMANOVA, a sphericity test will be performed to determine whether the data are suitable for analysis by RMANOVA. If the data do not conform to the conditions of sphericity condition, the degree of freedom will be corrected using factor ε before the RMANOVA is performed. The categorical measure of psychological status will be analyzed using either the rank-sum test or Spearman's rank correlation.4.Safety analysis: In accordance with the definition of adverse events, specific adverse events, their severity level, causes, and explanations will be listed. The number of adverse events, and the incidence of adverse event will be statistically described. If inter group comparison is required, the χ^2^ test or Fisher's exact test will be performed.5.Methods of statistical analysis: An independent statistician analyzed the outcome data in accordance with the principle of intention-to-treat (ITT), that is, all subjects recruited in the group will be covered. The analysis of efficacy and safety indicators will be conducted following the principle of per-protocol (PP), that is, all subjects who completed the whole trial process without major protocol violations will be included. All statistical analysis complied with ITT population, and the results of ITT analysis will be compared with PP analysis to assess the sensitivity. All missing data will be analyzed using the last observation carried forward (LOCF) interpolation method. The qualitative data will be tested for normality, according to which independent *t* test or Mann–Whitney *U* test will be performed for groups comparison. Qualitative variables will be presented by the statistical description of χ ± SD of the normal distribution data, whereas qualitative variables will be recorded as the number of cases in each category. If the quantitative variables constitute repeated measures data, RMANOVA will be adopted for comparison, and the sphericity test will be performed to ascertain the applicability of, as well as to correct the data. The categorical variables will be represented by numbers (percentages) by χ^2^ test or Fisher's exact test *P* < .05 will be considered statistically significant on both sides in all the statistical tests. SPSS 25.0 software (SPSS, SPSS Inc, Chicago, IL) will be adopted for data statistical analysis.

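### The elimination rule in section 2.6 conflicts with the intention-to-treat population promised in section 2.15.2, which also assigns the efficacy analysis to the per-protocol set

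*Protocol article*

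**What the plan says.** Section 2.6 (Elimination standard) opens with "Subjects will be eliminated from the trial if meeting any of the following conditions". Its eight items are:

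1. conversion to open surgery ("laparoscopy must be converted to laparotomy");
2. "refusal to continuous treatment for various reasons";
3. severe complications during treatment;
4. transfer to another specialty;
5. coma or death;
6. "cannot participate in the follow-up for various reasons";
7. mistaken inclusion;
8. reduced compliance combined with failure to supply critical information.

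Section 2.15.2 (Statistical analysis, item 5) makes three statements about who is analysed:

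- The outcome data are analysed "in accordance with the principle of intention-to-treat (ITT), that is, all subjects recruited in the group will be covered".
- Efficacy and safety indicators are analysed per protocol, in completers with no serious deviation.
- All analyses use the ITT population, and per-protocol results are compared with them as a sensitivity check.

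The same item applies last observation carried forward (LOCF) to all missing data. Item 1 asks for dropouts and their reasons to be described for each data set.

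The primary outcome (section 2.11.2) is one time per patient, from return to the ward to first flatus. The schedule in the Figure 2 legend runs to 2 weeks after discharge. Section 2.8 accepts that patients and acupuncturists cannot be blinded.

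**The concern.** A patient cannot be both removed from the trial and kept in an analysis of everyone recruited. The article does not say that eliminated patients stay under observation, that they remain in the ITT set, or that section 2.6 only defines the per-protocol set. Section 2.15.2 makes this worse by naming both ITT and per protocol for efficacy. An analyst could defend either population as primary.

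Three things are at stake.

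- **The primary comparison.** Refusal, complications and non-compliance occur after patients know their treatment. The treatments also differ in burden: head needles kept in for 6 h against one injection (section 2.10). If the eliminated patients recover bowel function later, and more of them come from one arm, that arm looks faster than it is.
- **Observed outcomes.** Under item 6, a patient who misses the contact 2 weeks after discharge could be removed although the flatus time was recorded in hospital.
- **Safety.** Section 2.12 wants complications recorded until 2 weeks after discharge, while section 2.6 eliminates patients who have severe complications or die.

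**Working it through.** **Step 1: the texts side by side.**

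| Question | Section 2.6 | Section 2.15.2 |
|---|---|---|
| Is a patient who refuses, has a severe complication or misses follow-up still in the trial? | No | Yes, under the ITT definition |
| Which set carries the efficacy result? | Not stated | Per protocol in one sentence, ITT in the next |
| What replaces a missing value? | Not stated | LOCF |

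The conflict needs no arithmetic.

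**Step 2: can LOCF repair it?** LOCF needs an earlier value of the same variable. Time to first flatus is measured once. A patient eliminated before first flatus has nothing to carry forward.

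**Step 3: can an observed outcome be lost?** Pilot mean flatus times were 16.31 h and 26.14 h (Introduction). Follow-up runs to 2 weeks after discharge. Item 6 does not say which follow-up it means, so read literally it covers patients whose primary outcome is complete.

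**Step 4: how many patients?** The plan allows 15% dropout: 78 × 1.15 = 89.7, which reproduces its 90 per arm. Over both arms, 0.15 × 180 = 27 patients. This is an overall allowance, not a forecast of elimination in either arm. Whether 78 follows from its own inputs is a separate matter and does not affect this point.

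**Step 5: possible size of bias (illustration).** The elimination fractions q₁ and q₂ and the delay D are my assumptions; the article gives none of them. With arm mean μ, fraction q eliminated, and eliminated patients D hours slower than retained ones, the retained mean m satisfies

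μ = (1 − q)m + q(m + D) = m + qD, so m = μ − qD.

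With no true treatment effect, the difference between retained means is −(q₁ − q₂)D.

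For the type I error I took the pilot SDs (2.21 and 3.53 h, section 2.15.1) as the SDs of retained patients, 90 randomised per arm, and a normal approximation. At 20% versus 10% eliminated, 72 and 81 patients remain and

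SE = √(2.21²/72 + 3.53²/81) = 0.471 h.

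| Eliminated (experimental / control) | D | False difference | Type I error (nominal 5%) |
|---|---|---|---|
| 15% / 15% | 4, 8 or 12 h | 0 | 5% |
| 20% / 10% | 4 h | 0.10 × 4 = 0.4 h | about 14% |
| 20% / 10% | 8 h | 0.10 × 8 = 0.8 h | about 40% |
| 20% / 10% | 12 h | 0.10 × 12 = 1.2 h | about 72% |

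The false benefit goes to the arm with more elimination. Against the 4 h target it is 10% to 30%. The 12 h row is generous: it is 12/3.53 = 3.4 times the larger pilot SD.

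**The case against.** The best defence is that section 2.6 was meant as a list of withdrawal criteria or as the definition of the per-protocol set. Section 2.15.2 defines both sets, compares them, and asks for dropouts and reasons by data set. No sentence says that data collection stops at elimination, and detailed handling of withdrawn patients is often left to a full protocol or SAP, which is not shown. The intervention is a single session and flatus comes within about a day in the pilot, so the window for elimination before the primary outcome is short. Much of this stands, and it limits the likely size of the problem. It does not remove the contradiction, because the article says elimination is from the trial, sets no narrower limit, and contradicts itself on which set carries efficacy.

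A reader might infer more than the documents support:

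- **That intraoperative criteria bias the comparison.** Operation time ("the operation time is 2 ± 1. 0 h"), blood loss ("with intraoperative blood loss ≥1000 mL or hemoglobin <70 g/L") and conversion are known only during or after surgery, and section 2.2 says "After signing the informed consent, subjects will be randomly split into two groups and received different treatment". That places allocation after consent, not before surgery. The Abstract speaks of inpatients who have already had their operation, and the flow and schedule figures are not shown. Even if allocation came first, treatment starts 30 min after surgery, so these events cannot result from it. Under concealed allocation they would mainly cost numbers.
- **That the bias could approach the whole 4 h target.** Taking 15% eliminated and a 24 h delay gives 0.15 × 24 = 3.6 h, but only if nobody is eliminated from the other arm. A 24 h delay is also 6.8 to 10.9 times the pilot SDs (24/3.53 and 24/2.21).
- **That poor responders, or all poorly compliant patients, are removed.** Poor response is not among the eight items, and item 8 requires both reduced compliance and missing critical information.

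**Conclusion.** The contradiction is established from the text alone. Section 2.6, followed literally, breaks the ITT analysis that section 2.15.2 promises. The per-protocol sentence leaves the primary population unclear, and LOCF cannot rescue an unobserved flatus time.

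Bias is a possibility, not a demonstrated result. It needs elimination that differs by arm in frequency or prognosis, which is plausible given unblinded participants and treatments of different burden. The 0.4 to 1.2 h range rests on assumed elimination of 20% versus 10% and an assumed delay of 4 to 12 h. With equal elimination and equal delay it is zero.

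The timing of allocation relative to surgery is an open question, not a fault shown by the documents.

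**What to change.** 1. Reword section 2.6 so that these items are recorded as protocol deviations or intercurrent events and serve only to define the per-protocol sensitivity set.
2. State that outcome and safety data continue to be collected where possible after any of these events, and that every randomised patient stays in the primary ITT analysis.
3. State that an observed flatus time is kept when later follow-up is missed.
4. Correct the per-protocol sentence in section 2.15.2 so that ITT is clearly primary and per protocol is the sensitivity analysis.
5. State when the envelope is opened. If that is before surgery, moving it to the interval after the intraoperative eligibility criteria are confirmed and before the intervention would avoid needless post-randomisation exclusions. If it already happens then, one clarifying sentence is enough.

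Items 1 to 4 cost a few sentences, plus the effort of continuing data collection in patients who would otherwise have been dropped. Item 5, if a change is needed, requires envelopes to be available at the end of surgery. None of this alters treatment or clinical management.
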